## Abstract

**Introduction:**

Dementia and Imagination is a multidisciplinary research collaboration bringing together arts and science to address current evidence limitations around the benefits of visual art activities in dementia care. The research questions ask: Can art improve quality of life and well-being? If it does make a difference, how does it do this—and why? Does it have wider social and community benefits?

**Methods and analysis:**

This mixed-methods study recruits participants from residential care homes, National Health Service (NHS) wards and communities in England and Wales. A visual art intervention is developed and delivered as 1×2-hour weekly group session for 3 months in care and community settings to N=100 people living with dementia. Quantitative and qualitative data are collected at 3 time points to examine the impact on their quality of life, and the perceptions of those who care for them (N=100 family and professional carers). Repeated-measures systematic observations of well-being are obtained during the intervention (intervention vs control condition). The health economics component conducts a social return on investment evaluation of the intervention. Qualitative data are collected at 3 time points (n=35 carers/staff and n=35 people living with dementia) to explore changes in social connectedness. Self-reported outcomes of the intervention delivery are obtained (n=100). Focus groups with intervention participants (n=40) explore perceptions of impact. Social network analysis of quantitative and qualitative data from arts and healthcare professionals (N=100) examines changes in perceptions and practice.

**Ethics and dissemination:**

The study is approved by North Wales Research Ethics Committee—West. A range of activities will share the research findings, including international and national academic conferences, quarterly newsletters and the project website. Public engagement projects will target a broad range of stakeholders. Policy and practice summaries will be developed. The visual art intervention protocol will be developed as a freely available practitioners guide.

Strengths and limitations of this studyDementia and Imagination is the largest arts and dementia research study in the UK.The development and delivery of the research involves partnerships between universities, community arts organisations, galleries, the National Health Service (NHS) and charities.It combines methods and practice from health and social sciences together with the arts and humanities to address a key societal challenge—supporting the quality of life (QoL) of the growing number of people living with dementia.A limitation is that this mixed-methods study design cannot focus on a more robust test of effectiveness (eg, as a randomised controlled trial would) as this was beyond the available resources.

## Introduction

### Background

There is no cure for dementia, therefore attempts to maintain QoL and well-being for those living with memory difficulties are crucial. Dementia is now firmly on the international public and policy agenda, bringing opportunities for change on a wider scale for those living with the condition^1^ and the communities in which they live. In the UK, changing awareness and understanding about dementia and enabling people to ‘live well’ is central to the National Dementia Strategy.^2^ Creating dementia supportive or dementia friendly communities is a major policy objective and a societal imperative noted in the National Dementia Vision for Wales^3^ and the Prime Minister's Challenge on Dementia.^4^

There is substantial interest in the role of the arts in dementia care, largely driven by innovative practice. Arts-based activities include dance, music, theatre, creative writing, visual art and singing. Reviews of arts and dementia research suggest a range of positive benefits to those taking part, such as improvements in well-being, QoL, cognitive function and communication.^5–10^ However, associated research in this area has not kept pace, limiting the extent to which science informs practice and service improvement. All the reviews highlight methodological issues, which limit the impact of findings.^5–10^ In particular, most of the published research around visual art programmes for people living with dementia have used small or opportunist samples of people. Belfiore and Bennett^11^ argue the rhetoric around the cultural, social and health benefits of arts is often derived from unquestioned, deep-seated beliefs about the role and functions of the arts in society which have become widely accepted. Nevertheless, longitudinal population studies suggest that cultural activities can have a positive impact on health.^12^

### Summary of current study

The Dementia and Imagination research is a multidisciplinary collaboration, bringing together arts and science to address current evidence limitations. The development and delivery of the research involves partnerships between universities, community arts organisations, galleries, the National Health Service (NHS) and charities. The research combines methods and practice from health and social sciences together with the arts and humanities to address a key societal challenge—supporting the QoL of the growing number of people living with dementia. It is a large programme of work, using the medium of visual art as an exemplar and catalyst for change. It examines the beneficial impact of taking part in art activity on the QoL of people living with dementia, together with the cost-benefit, and the perceptions of those who care for the participants living with dementia. More broadly, through public engagement and research dissemination activities it uses artistic output from the study, and artistic interpretations of the data and methods, together with quantitative and qualitative data to challenge the public perception of dementia. It examines processes of delivering the intervention and outcomes to advance understanding and be of value to research, policy and practice. Online supplementary appendix 1 presents the different components of the study, set out as work packages. This paper describes the data collection methods and analyses for the different groups of participants. The research started in July 2013, and is due to complete February 2017.

10.1136/bmjopen-2016-011634.supp1supplementary appendix

### Rationale

As previously noted, reviews of arts activities suggest a number of positive benefits. There is currently no evidence to suggest that one art form is more appropriate or beneficial than another in terms of psychosocial outcomes for people living with dementia. This research focuses on visual art activities as a starting point in expanding the evidence base. It builds on small scale but appropriately conducted exploratory studies delivered in galleries, museums and care settings, which suggested some positive outcomes for people living with dementia taking part in visual art programmes.^13–15^ From a theoretical perspective, visual art programmes may be beneficial for people living with dementia. It is suggested that the experience of visual art-based participation can provide marginalised people creative ways to represent their experiences and extend communication and facilitate social interaction.^13–15^ Visual art forms such as pictures, photos and sculptures endure and can be used in a variety of situations or exhibitions to demonstrate that people with dementia can accomplish and learn new things, despite limited mobility or cognition.^16^ In turn, the artefact can provide cognitive stimulation. However, with the exception of a qualitative study of a gallery-based intervention,^i^^17^ there has been little research or theorising about the underlying theoretical mechanisms through which benefits develop and are sustained.^6^
^18^ Consequently, the theoretical basis underlying efficacy is investigated in this research. This informs the development of the visual arts intervention, delivered in three settings (community venues, residential care and NHS inpatient wards) and evaluated at three points in time.

Many people with dementia wish to participate in activities, feel valued and have a sense of purpose.^19^ They wish to remain within their communities, in the home of their choice, near their family, carers and friends.^20^ In other words, they wish to remain socially connected. Socially inclusive societies are important for the QoL of people living with dementia.^3^
^4^ However, the social representation of dementia often has a stigmatising effect on everyday interactions for both the person with dementia^21^ and their carer or partner. The general public often has a narrow and negative way of conceptualising dementia.^22^ In the face of this adversity, people with dementia (and their carers) can become disconnected, marginalised and excluded from society. Many people with dementia have minimal or no access to good quality intellectual or sensory activities, and those that do exist are often much below the person's level of functioning.^14^ This research examines the disconnection commonly experienced in dementia, and changes in social connectivity that can be facilitated by a stimulating visual arts intervention.

The stereotypes and stigma associated with dementia as previously described contributes to creating a pervasive, negative attitude known as excess disability, the tendency to attribute more disease or condition-associated impairment than the actual capabilities of the person with dementia.^23^ However, social networks have the potential for influencing behaviour and attitudes and this effect is described as social contagion.^24^ Thus, further aims of this research are to (1) use social network analysis to understand the social contagion through the implementation of good practice throughout the artists and practitioners involved in the project and beyond and (2) examine changes in perceptions and beliefs about people with dementia in the social networks of artists and professional carers of people with dementia.

The evidence review by the Mental Health Foundation^8^ noted that the community impact of arts activities has received little attention; however, activities have the potential to break down stereotypes, reduce stigmatising behaviour, foster social cohesion and raise awareness within the wider community. Creative outputs have the potential to counter stereotypes that often assume that people with dementia are unable to express their individuality in a way that is understood by others.^25^ Visual outputs can be used in creative ways to engage the public about health-related issues.^26^ Thus, public engagement activities will be a key focus in the final stages of the research.

The research programme addresses the following objectives:
To develop a theoretically informed visual arts intervention;To examine the impact of the visual arts intervention on the social connectedness, QoL and well-being of people living with dementia;To examine family and professional carers attitudes towards dementia, and whether they change through their exposure to the visual arts intervention;To examine the cost–benefit of the visual arts intervention;To explore qualitative changes in social connectedness and communication at the microlevel between the participant and formal or informal carer(s) and other network members;To undertake public engagement activities, challenging perceptions of dementia;To understand the implementation of arts and health research, exploring the extent to which ‘messages of change’ spread through professional networks—social contagion;To maximise the impact of the study for policy, practice and further research.

## Methods and analysis

### The visual arts intervention

This research builds on art viewing and making programmes for people with dementia developed by some major art galleries (eg, Museum of Modern Art, New York; the Royal Academy, London; Dulwich Picture Gallery, London; National Gallery of Australia, Canberra; and Nottingham Contemporary). These take on a variety of forms of art viewing and art making, such as exploring the art history of an artwork and at other times using it as the starting point for creative discussion. They usually involve small groups of people meeting weekly.

### Intervention development

Visual art programmes are by their nature ‘complex’ in that they contain several independent interacting components (eg, settings, people receiving and delivering, their behaviours and responses, etc) which create difficulty in understanding what the ‘active ingredients’ are that bring about changes in outcomes.^27^ Complex interventions are often implemented in a diverse manner by people with variations in skills and ability, to different populations in different settings, which can influence the outcome of the intervention.^28^

The intervention development phase aims to uncover the ‘active ingredients’ to help understand how visual art interventions might be effective. This involves three approaches to theory development: (1) a realist synthesis, (2) workshops with artists, and (3) a survey of arts organisations, people with dementia and their carers. (1) A realist synthesis of published research enables an understanding of how and why something might be effective. It is used for theory development and to facilitate implementation into practice.^28^ The research team will use this approach to inform the development of the arts intervention. To the best of our knowledge, this novel approach has not previously been undertaken. The synthesis protocol is published and publicly available.^29^ (2) Workshops with stakeholders and artists (up to 40) will explore their practice to understand ‘what works’ from their perspectives. (3) A survey of organisations delivering arts programmes, people with dementia and their carers who have previously participated in similar activities, to explore what they feel worked best, and why and what was not good practice. An overarching synthesis of these three phases will produce a conceptual model to inform the visual arts intervention and a practitioners' manual (best practice guidelines for delivering the visual arts intervention), which will be finalised and publically available after the data analysis. Key aspects of the practitioners' manual form the basis of a fidelity checklist. Artists' practice is assessed from video analysis of the intervention at the beginning and end of the programme.

It is anticipated that the intervention activities will be participative and the emphasis will be on providing a stimulating, high-quality experience for the participants that require no prior knowledge or experience/skills. It will aim to encourage creativity without overwhelming people with complex instructions, be interesting and challenging, but not requiring advance artistic skills. It will encompass meaningful engagement that can stimulate imagination and discussion, not lectures or the generation of factual exchanges that rely on memory for names and dates. It will provide some structure, but create the opportunity for individual expression in a failure-free environment. For some activities, we will engage carers and staff alongside the participants.

### Study sites

There are three study sites with distinct settings: site 1, residential care facilities in the North East of England; site 2, NHS hospital wards in Derbyshire; site 3, community venues in North Wales. These settings provide different cultural contexts (eg, different industrial histories, languages and organisational practices, urban and rural contrasts) and different residential and employment locations of the participants.

### Intervention delivery

In each of the three study sites, the community arts partners (Equal Arts, Nottingham Contemporary and Denbigh County Council Community Arts) will recruit artists or use existing artists and lead the delivery of the intervention programme. These key partners have been involved in the codesign of this research from its inception, and have considerable experience of running art programmes for people with dementia and their carers. All artists will attend training provided by the research team, covering research procedures, ethics and governance. In each data collection site, the programme is delivered in a group format (estimate up to 12 people per group) as four staggered waves of 3 months duration each. The participants within each area will attend one group session a week of up to 2 hours duration.

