### Participants

#### Sample size

We will recruit up to 100 participants with dementia and 100 staff and carers across three data collection sites. Attrition is expected with dementia research. To counter this possibility, we will aim to over-recruit by up to 25%. It is estimated that a 95% confidence level with 5% margin of error would require N=80. We recognise that if we were running a clinical trial of effectiveness, then the number of people with dementia required would be much larger. Numbers are chosen pragmatically, reflecting the feasibility of recruitment rates within the timescale and resources of the research programme. However, this work is the first step towards a more definitive study. For a psychosocial intervention that is not a full clinical trial (as is this arts programme), this is a relatively large number of people with dementia and yields useful process data for a future, definitive study.

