##### Associated measures for people living with dementia

Clinical Dementia Rating Scale:^34^ administered at T1 only, to establish severity of the symptoms of dementia, completed by researcher.Dementia Quality of Life:^33^ a 31-item measure of QoL designed for carers of people with dementia (to be completed by carer or staff).Holden Communication Scale:^35^ assesses a range of social, behaviour and communication variables (to be completed through discussion with carer or staff member).

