##### Focus groups with people living with dementia

In each of the data collection areas a short, postsession focus group is held in the last month of the intervention period with each of the intervention groups (up to 4 in each area, 12 in total). This will only be for the participants with dementia, to ensure that any effects that are experienced ‘in the moment’ are verbalised from their own perspectives. This session is led by the researcher and will be videoed or audio recorded for research purposes only, the video/audio recording is not to be made public or shared beyond those involved in the analysis.

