#### Primary outcomes

Change over time (T1 and T2 and longer term T3) for significant improvements in the Dementia Quality of Life Scale (DEMQOL) and Holden Communication Scale will be ascertained using a repeated measures mixed-effects model. It will examine the extent to which the number of sessions attended, location, age, gender, education, socioeconomic status, medication use, Clinical Dementia Rating Scale (CDR) score and location are associated with outcomes. Differences between the three settings will be tested. Should these not be significant, data will be combined to increase sample size. Change over time in observed well-being between times 1 and 2, and differences between the control and intervention will be examined with a repeated measures mixed-effect model.

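### Delivery is in up to 12 art groups but the primary model names no group term; if group is omitted and change varies between groups, standard errors for change will be too small

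*Protocol article*

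**What the plan says.** Under Intervention delivery, the article states of every site that "the programme is delivered in a group format (estimate up to 12 people per group) as four staggered waves of 3 months duration each". In the focus-group section the same count appears from another direction: a session is held "with each of the intervention groups (up to 4 in each area, 12 in total").

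Under Analysis of study sample 1, Primary outcomes, change in DEMQOL and the Holden Communication Scale across T1, T2 and T3 "will be ascertained using a repeated measures mixed-effects model". The terms listed are attendance, demographic and socioeconomic variables, medication, CDR score and location. The three settings are to be compared, and the data combined if they do not differ significantly. Art group, wave, artist, care home and ward are not among the named terms. The random-effects structure is not given.

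On numbers, Sample size says: "We will recruit up to 100 participants with dementia and 100 staff and carers across three data collection sites". It adds: "It is estimated that a 95% confidence level with 5% margin of error would require N=80". It describes the numbers as pragmatic and says the study is not a trial of effectiveness.

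**The concern.** People in one art group share an artist, sessions, companions and a calendar period. The article itself says, under Intervention development, that complex interventions are delivered by people of differing skill and that this can influence the outcome. It is therefore plausible that mean change differs from group to group, and a term for location would not absorb differences in change between groups within a site.

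This matters more here than in a controlled comparison. The control condition applies only to the observed well-being measure. For DEMQOL and Holden the time effect is the whole basis for claiming improvement, so between-group variation in change goes straight into its error. If the model treats people as independent given their own repeated measures, confidence intervals are too narrow and p-values too small. The combining rule adds to this: it regards the person as the unit of information and could drop location, the only higher-level term named.

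**Working it through.** **The plan's own figure.** N=80 can be reproduced as a survey sample size for a proportion with a finite-population correction. The article gives neither p = 0.5 nor a population of 100; both are assumptions made here.

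- n0 = 1.96² × 0.25 / 0.05² = 384.1
- n = 384.1 / (1 + 383.1/100) = 79.5, rounded up to 80

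This figure does not concern change in DEMQOL or Holden and makes no allowance for clustering. The check below uses 80 only as a number of people analysed.

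**Inputs.**
- Groups: four per area in three areas, 12 in total (Focus groups section). This is a maximum.
- People: 80 (the stated requirement) or 100 (the recruitment ceiling), so m = 80/12 = 6.67 or 100/12 = 8.33 per group. The article itself gives only a maximum of 12 per group.
- ICC of change within art group: not in the article. The range 0.01 to 0.10 is assumed.

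**Formulas.** Design effect DE = 1 + (m − 1) × ICC. The true standard error is √DE times the one reported when group is ignored. The true error of a nominal two-sided 5% test is 2 × [1 − Φ(1.96/√DE)].

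| People | ICC of change | DE | √DE | True error |
|---|---|---|---|---|
| 80 | 0.01 | 1.06 | 1.03 | 5.7% |
| 80 | 0.05 | 1.28 | 1.13 | 8.4% |
| 80 | 0.10 | 1.57 | 1.25 | 11.7% |
| 100 | 0.01 | 1.07 | 1.04 | 5.9% |
| 100 | 0.05 | 1.37 | 1.17 | 9.4% |
| 100 | 0.10 | 1.73 | 1.32 | 13.7% |

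Example for 80 people at ICC 0.05: 1 + 5.67 × 0.05 = 1.28; √1.28 = 1.13; 1.96/1.13 = 1.73; two-sided tail 8.4%.

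**Simulation check.** The set-up was 12 groups of 8, two time points and a paired analysis that recognises only the person, with 20,000 replicates.
- Group-by-time variation, ICC of change 0, 0.02, 0.05 and 0.10: type I error 5.2%, 6.4%, 9.4% and 12.9%.
- Group variation in level only, constant over time, with variance 0.05, 0.10 and 0.20 (person variance 0.6, residual 0.4): type I error 5.0%, 5.2% and 4.9%.

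A stable group effect cancels from within-person change. Only differences between groups in change cause the problem.

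**The case against.** The strongest reply is that this is silence in a condensed article. Calling the model mixed-effects neither includes nor excludes a group effect, and random effects are often left to a fuller document. A reader might infer that the model handles only repeated measures within a person and that the standard errors are therefore too small. The article supports neither statement outright: the first is not written, and the second also requires that change varies between groups, for which no ICC is given. That part of the objection stands, and the conclusion is conditional for that reason.

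It does not dispose of the point. The article names the model type, lists its terms and fixes a combining rule. Repeated measures is the only dependence it mentions.

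The word location is also ambiguous. Under Study sample 3 it is used for individual venues such as care homes and villages, so it may capture part of the within-site variation. A location main effect would still not account for group differences in change.

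A reader might go further and infer that one staff member rates several residents, since Holden is "to be completed through discussion with carer or staff member", and ask for an informant random effect. The article does not say that raters are shared, and it recruits 100 staff and carers alongside 100 people with dementia. A rater's stable leniency would cancel from change if the same rater is used throughout. Another variance component would also be hard to support with about 80 people.

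Finally, the study disclaims a test of effectiveness. That limits how serious the point is, but the plan still looks for significant improvements and presents itself as a step towards a definitive study.

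**Conclusion.** The point holds conditionally. Delivery is in up to 12 groups, and the stated primary model names nothing below location that would represent them. If group is omitted from the final model and change in DEMQOL or Holden varies between groups, standard errors for change are too small. For 80 people in 12 groups the factor is about 1.13 (true error about 8%) at an assumed ICC of change of 0.05 and about 1.25 (about 12%) at 0.10. At 0.01 it is negligible and at zero there is none. With 100 people the effect is somewhat larger.

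These sizes rest on the assumed ICCs, on all 12 groups running, and on roughly equal group sizes. This is a worthwhile improvement to the analysis; it does not show that the results will be invalid.

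**What to change.** In Analysis of study sample 1, Primary outcomes, state that the time effect will account for art group. Use random group and group-by-time effects with small-sample degrees of freedom. If the group-by-time variance is estimated at its boundary, use group-robust standard errors with a small-sample correction instead. Keep the group structure whatever the test between settings shows. Report the estimated group ICC of change with its uncertainty, because the definitive trial will need it for its sample size. No informant random effect is needed.

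The cost is a change of analysis wording and no extra data beyond recording group membership. With 80 people, confidence intervals widen by about 13% to 25% at an ICC of 0.05 to 0.10, before any further widening from the small-sample degrees of freedom. A variance estimated from at most 12 groups will be imprecise, and the report should say so.
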